### Ethical declarations

The study will be conducted in compliance with the protocol, principles of good clinical practice (ICH-GCP), Regulation (EU) No 536/2014, and in accordance with the ethical principles put forward in the second Declaration of Helsinki. The study is GCP monitored and has been approved by the Danish Medicines Agency and Ethical Committee (EU CT number 2023-503297-20-00). Oral and written consent from patients is mandatory and collected before any study-related procedures are performed.

### Statistics

Demographic data will be presented with range and median where appropriate.

#### Interim analysis

The reported risk of serious complications during standard thoracoscopy is approximately 5 % [30, 31]. Based on our preliminary experience with PITAC and the limited data from the literature, the risk of adding PITAC to a standard thoracoscopy seems low. However, since the actual risk of PITAC is unknown, we choose to perform an interim safety analysis after every 10 procedures. The study will be discontinued if four or more procedures have led to patients having Clavien-Dindo ≥ 3b or CTCAE≥4 complications/adverse events.

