**Methods:**

The prospective, controlled, phase-I study is designed to treat MPE with PITAC. There are no data to support the estimated number of patients needed, but previous experience estimates the non-access rate to 20 %. Twenty eligible patients with MPE will receive two or more PITACs at four-week intervals. During video-assisted thoracoscopy, MPE and/or pleural lavage fluid is evacuated, and the extent of visible PLM is assessed. Pleural biopsies are collected, if possible, for histological response as per Thoracic Regression Grading Score (TRGS). Patients are screened for treatment-related intra- and postoperative complications. The primary outcome is the number of patients with Clavien-Dindo ≥3b or Common Terminology Criteria for Adverse Events≥4 within 30 days. Secondary objectives include PLM-score, TRGS and cytology, length of hospitalization, personnel safety, quality of life, and change in MPE volume.

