#### Primary and secondary objectives

This is a Phase-I study investigating safety and feasibility of repeated PITAC (minimum of two procedures) in 20 patients. PITAC is considered feasible and safe if four patients or less have severe surgical complications defined as Clavien-Dindo ≥ 3b or life-threatening adverse events (AE) defined as Common Terminology Criteria for Adverse Events v. 6.0 (CTCAE) ≥ 4 within 30 days after the procedure. All medical AEs and surgical complications will be recorded, but only those who are probably or certainly/definitely related to the PITAC directed treatment will provide grounds for assessing the feasibility and safety.

Secondary objectives include (1) macroscopic evaluation of PLM before and after PITAC and evaluation of histological response using a proposed Thoracic Regression Grading Score (TRGS) in biopsies from visible PLM and MPE [23], (2) evaluation of response by pleural lavage fluid (PLF) or MPE cytology, (3) assessment of personnel safety (environmental and biological), and (4) evaluation of the quality of life with EORTC-QLQ-C30 at baseline, day 30 and three months after the last PITAC directed treatment.

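### The stopping rule (four or more procedures) and the safety verdict (four or fewer patients) overlap at four, so one result can mean both discontinue and safe.

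*Protocol article*

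**What the plan says.** The protocol article prints two study-level safety rules for events of the same grades (Clavien-Dindo 3b or higher, or CTCAE 4 or higher).

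- **Final verdict** (Primary and secondary objectives): "PITAC is considered feasible and safe if four patients or less have severe surgical complications" or life-threatening adverse events, counted "within 30 days after the procedure". On attribution, "only those who are probably or certainly/definitely related to the PITAC directed treatment will provide grounds for assessing the feasibility and safety". The abstract uses the same unit: "The primary outcome is the number of patients with Clavien-Dindo" 3b or higher, or CTCAE 4 or higher.
- **Stopping rule** (Interim analysis): "we choose to perform an interim safety analysis after every 10 procedures", followed by "The study will be discontinued if four or more procedures have led to patients having Clavien-Dindo" 3b or higher, or CTCAE 4 or higher, events. This section gives no grade of relatedness, time window or denominator. It does not say whether the four are counted from the start of the study or within each block of ten.

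The same section gives a reference figure: "The reported risk of serious complications during standard thoracoscopy is approximately" 5%. Each patient is to have two or three procedures (Study intervention and procedures). Recruitment continues until 20 patients have had at least two (Sample size). Among completers that makes 40 to 60 procedures.

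**The concern.** One rule ends the study at four or more; the other declares success at four or fewer. The first counts procedures and the second counts patients, but the two counts are tied, because a patient cannot be affected without an affected procedure. The value four can therefore fall on both sides.

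The final rule is the verdict on the primary outcome of a safety study, and the interim rule is the only study-level stop that the article shows. If the data land on the overlap, the investigators would have to decide after seeing them whether the study should have been discontinued or had shown PITAC to be safe. The missing counting rule adds to this, since the stop behaves very differently under the two possible readings.

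**Working it through.** **Logic, with no assumed risk.** Let X be the number of affected patients and Y the number of affected procedures. Each affected patient has at least one affected procedure, so Y ≥ X. The verdict is safe if X ≤ 4, and the study stops if Y ≥ 4.

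- Cumulative count: X = 4 gives Y ≥ 4, so both rules are met.
- Per block of ten: both rules are met if X = 4 and all four fall in the same block.
- With repeat events in one patient, X = 2 or 3 can also reach Y = 4. This should be rare, because the recruitment section lists severe events as a reason to discontinue a subject.

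The same number is also a different rate in each unit: 4/20 = 20% of patients, but 4/40 = 10% or 4/60 = 6.7% of procedures.

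**Size.** The article gives no error rate or derivation for either limit, so there is no figure to reproduce. Inputs: 20 patients; k = 2 or 3 procedures each, so N = 40 or 60; and an assumed risk q per procedure. The base case is q = 5%, borrowed from the thoracoscopy figure. Procedures are treated as independent, and no patient leaves early.

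Patient risk: P = 1 − (1 − q)^k. At q = 5%, P = 1 − 0.95² = 9.75% for k = 2, and 1 − 0.95³ = 14.26% for k = 3.

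Exactly four of 20 patients: 4845 × P⁴ × (1 − P)¹⁶.
- k = 2: 4845 × 0.0975⁴ × 0.9025¹⁶ = 8.5%
- k = 3: 4845 × 0.142625⁴ × 0.857375¹⁶ = 17.1%

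The other columns use:
- Safe: Pr(Bin(20, P) ≤ 4).
- Stop, cumulative: Pr(Bin(N, q) ≥ 4).
- Stop before the last look: the same with N − 10 procedures.
- Stop, per block: 1 − (1 − b)^(N/10), with b = Pr(Bin(10, q) ≥ 4). At q = 5%, b is about 0.001.

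| q | k | Exactly 4 patients | Safe (≤ 4 patients) | Stop, cumulative | Stop before last look | Stop, per block |
|---|---|---|---|---|---|---|
| 5% | 2 | 8.5% | 96.1% | 13.8% | 6.1% | 0.4% |
| 5% | 3 | 17.1% | 85.4% | 35.3% | 24.0% | 0.6% |
| 10% | 2 | 21.7% | 67.3% | 57.7% | 35.3% | 5.0% |
| 10% | 3 | 16.6% | 33.4% | 86.3% | 75.0% | 7.4% |
| 15% | 2 | 15.8% | 31.1% | 87.0% | 67.8% | 18.5% |
| 15% | 3 | 4.4% | 6.6% | 98.5% | 95.4% | 26.5% |

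The whole overlap under a cumulative count (X ≤ 4 and Y ≥ 4) at q = 5% is 9.9% for k = 2 and 20.7% for k = 3. Exactly four patients supplies 8.5 and 17.1 points of this. Fewer than four patients with repeat events supplies the remaining 1.4 and 3.6 points.

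**The case against.** The strongest reply is that the rules have different jobs. The verdict is framed for 20 patients with repeated PITAC, and a study stopped early does not reach 20, so the verdict would not be applied. On that view both rules bite on the same complete data mainly when the fourth event appears at the last look. This narrows the live conflict but does not remove it: the article does not say that a stop cancels the verdict, and a fourth event in the last block still meets both rules.

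Several stronger readings are tempting, and the document does not support them.

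- **A reader might infer that the real success limit is three.** That needs a cumulative count. The rule follows directly on the ten-procedure schedule and can be read as four per block. Then four patients spread over several blocks trigger no stop, and a verdict of safe with four is reachable.
- **A reader might infer that the stopping rule ignores relatedness.** Its wording is causal, since the procedures must have led to the events. The general sentence on attribution in the objectives section may also cover interim assessments. The grade of relatedness is unstated at the interim; it is not flatly contradicted.
- **A reader might set the 86.3% stopping chance (10% risk, 60 procedures) against the success limit of 20% of patients.** With three procedures each, a 10% risk per procedure is a 27.1% patient risk, above that limit, so frequent stopping is no anomaly. The risk per procedure that matches 20% of patients is 1 − 0.8^(1/3) = 7.2%.
- **A reader might call a fixed limit of four at every look an error.** A fixed cap is a simple design choice, and it contradicts nothing in the article.

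**Conclusion.** The point holds as a contradiction between two printed decision rules. Under a cumulative count, exactly four affected patients means both discontinue and safe. Under a per-block count this happens when the four fall in one block. That conclusion rests on the text and needs no assumed risk.

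The size does depend on assumptions. At 5% per procedure, the main contradictory result under a cumulative count has probability 8.5% to 17.1%. At that same risk the final rule would say safe with probability 96.1% to 85.4%. The unstated way of counting moves the chance of meeting the stopping limit from 13.8%–35.3% (6.1%–24.0% before the last look) to 0.4%–0.6%. The 5% is quoted for serious complications of standard thoracoscopy and may not use the trial's event definition, so these figures illustrate scale and do not predict. Independence between procedures, and no patient leaving after a severe event, are also assumed.

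The difference in unit adds little by itself. The conflict comes mainly from both rules including the value four.

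**What to change.** Amend the objectives and Interim analysis sections together so that no result meets both rules:

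- use one unit (patients or procedures), one relatedness rule and one time window in both places;
- state whether the interim count is cumulative or per block of ten;
- state which rule prevails at four, and whether the final verdict applies to a study that has been stopped;
- report the operating characteristics of the reconciled rules, meaning the chance of stopping and the chance of a safe verdict over a range of assumed risks.

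The limits are for the sponsor to choose, and none is proposed here. The cost is one paragraph of amendment, with no extra patients, visits or data. The downside is that the stated safety limit may become slightly less favourable.

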Patients will be excluded from the study if (1) requested by the patient, (2) access to the pleural cavity is not possible due to adhesions or other technical aspects, and/or (3) decline in general health resulting in Eastern Cooperative Oncology Group (ECOG) performance status higher than 2. Following events are considered sufficient reasons for discontinuing a subject from the study (1) withdrawal of consent, (2) death, (3) loss to follow up and/or (4) severe AE or surgical complications. The following information will be recorded for patients who have been excluded from the study: Survival, amount and frequency of MPE drainages and illness specific variables (e.g. CT-scan results).

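### The feasible-and-safe verdict counts a PITAC-related death like any other qualifying event, so up to three related deaths with no other such event would pass it without reaching the mandatory stop limit

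*Protocol article*

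**What the plan says.** All references are to the protocol article.

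- **Primary outcome** (Abstract, Methods): "The primary outcome is the number of patients with Clavien-Dindo ≥3b or Common Terminology Criteria for Adverse Events≥4 within 30 days". Deaths have no separate count.
- **Final verdict** (Primary and secondary objectives): "PITAC is considered feasible and safe if four patients or less have severe surgical complications defined as Clavien-Dindo ≥ 3b". A medical event on the other scale, at grade 4 or above in the same 30-day window, counts towards this limit as well; the cut is again open at the top.
- **Relatedness filter** (same section): "only those who are probably or certainly/definitely related to the PITAC directed treatment will provide grounds for assessing the feasibility and safety". A death attributed to PITAC passes this filter.
- **Stop rule** (Statistics, Interim analysis): "The study will be discontinued if four or more procedures have led to patients having Clavien-Dindo ≥ 3b or CTCAE≥4 complications/adverse events". On timing: "we choose to perform an interim safety analysis after every 10 procedures".
- **Death named as an event** (Recruitment process, in the text on exclusion and discontinuation): "Following events are considered sufficient reasons for discontinuing a subject from the study (1) withdrawal of consent, (2) death". This ends one subject's participation and says nothing about the study as a whole.

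**The concern.** The stated aim is to evaluate patient and personnel safety, and the interim section concedes that the actual risk of PITAC is unknown. The headline conclusion will be the yes/no verdict in the objectives section. That verdict depends only on how many patients cross one severity cut, not on how far they cross it. A series with three fatal PITAC complications and a series with three non-fatal complications that just meet the cut get the same label.

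At stake is a published statement that PITAC is safe, which the authors expect to shape the next steps in implementation, alongside a related mortality that few readers would call safe. The article also prints nothing that brings a safety look forward after a related death. The only study-level check it describes is the one after each block of 10 procedures.

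**Working it through.** The article gives no alpha, power, target rate or mortality rate, so there is no stated figure to reproduce. The check is a direct reading of the two limits, followed by exact binomial arithmetic.

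**Inputs from the article**
- Stop limit: 4 or more procedures with an event.
- Verdict limit: 4 or fewer patients with an event.
- 20 patients completing at least two procedures (Sample size); two to three procedures each (Study intervention and procedures). That is 20 × 2 = 40 to 20 × 3 = 60 procedures in completers.
- Serious complications of standard thoracoscopy: about 5% (Interim analysis).

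**Step 1: how many related deaths pass both rules?** A patient dies once, so if each death is attributed to one procedure, d deaths with no other qualifying event give d patients and d procedures.

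| Related deaths, no other event | Stop limit (≥4 procedures) | Verdict limit (≤4 patients) |
|---|---|---|
| 1 | not reached | met |
| 2 | not reached | met |
| 3 | not reached | met |
| 4 | reached | met |

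Three is the largest number that passes both. Timing does not matter: three deaths in the first 10 procedures also stay below four.

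**Step 2: what mortality does that represent?** If all three are among the 20: 3/20 = 15%, Clopper-Pearson 95% CI 3.2% to 37.9%. Per procedure: 3/40 = 7.5% (1.6% to 20.4%) to 3/60 = 5.0% (1.0% to 13.9%).

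**Step 3: how easily is the verdict limit met?** Assume a true related fatality of 15% per patient and no other events. P(X ≤ 4), X ~ Bin(20, 0.15), is 83%. This concerns the verdict limit alone; a run with exactly four deaths would also have reached the stop limit.

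**Step 4: how does the stop limit behave?** P(X ≥ 4) = 1 − Σ(k = 0 to 3) C(n,k) p^k (1−p)^(n−k), with independent procedures. The death risks of 2% and 5% per procedure are assumptions. The right-hand columns add an assumed 5% of other qualifying events, borrowed from the article's thoracoscopy figure, so p = 0.02 + 0.05 = 0.07 and p = 0.05 + 0.05 = 0.10.

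| Assumed death risk | Deaths only, n = 40 | Deaths only, n = 60 | Plus 5% other, n = 40 | Plus 5% other, n = 60 |
|---|---|---|---|---|
| 2% | 0.8% | 3.2% | 30.6% | 61% |
| 5% | 13.8% | 35.3% | 57.7% | 86% |

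Put differently, given three deaths in 40 procedures, the chance that at least one of the other 37 has a qualifying event is 1 − 0.95^37 = 85% at a 5% event risk, or 1 − 0.98^37 = 53% at 2%. Either would bring the count to four. How far the stop limit responds therefore depends mostly on what is assumed about non-fatal events.

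**The case against.** **The full protocol may deal with a fatal event.** An article commonly leaves unscheduled review, temporary halts and regulator notification to it, and the ethics section cites ICH-GCP, GCP monitoring and Regulation (EU) No 536/2014. This stands for the stop side, and the fix is conditional on it. It does not reach the verdict, whose rule is printed and contains no reservation for deaths.

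**The stop rule is a trigger, not a licence to continue.** A reader might infer that the study has to carry on after three deaths, or that the stop rule can hardly react to deaths at all. The article supports neither. The rule says when the study will be discontinued, not that it may be discontinued only then, and the sample size section says the interim analyses exist to monitor patient safety. The very low stopping probabilities appear only if deaths are the sole severe events. With other qualifying events at an assumed 5%, they rise to 30.6% and 57.7% at 40 procedures.

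**The 15% depends on the denominator.** Recruitment runs until 20 patients have completed two procedures, so a patient who dies after the first may not be one of the 20. This is correct: 3 of 20 is one scenario, and the article does not settle which patients form the denominator.

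**A single severity cut is a legitimate design choice, and deaths are not hidden.** All adverse events are to be recorded, and survival is tracked even for excluded patients. That is also true. But recording a death does not alter the label that the verdict rule assigns.

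**The article prints no grading table for either scale.** The reading that deaths fall inside the counts rests on the open-ended cuts. If deaths fell outside them, the rules would ignore deaths entirely, which would be no better.

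**Conclusion.** The point holds for the verdict, and in a limited form for the interim rule. As printed, one, two or three related deaths with no other qualifying event satisfy the feasible-and-safe criterion without reaching the mandatory stop limit. At the extreme this is 3 of 20, or 15% (exact 95% CI 3.2% to 37.9%).

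This rests on three conditions: the deaths are judged probably or definitely related, no further procedure leads to a qualifying event, and all three patients are counted among the 20. If one more procedure qualifies, the stop limit is reached. On the interim side, all that can be said is that the article prints no provision for an earlier look after a related death; whether the full protocol has one cannot be told from this text. The size of the four-event limits is not in question here.

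**What to change.** Keep both four-event limits.

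1. **Primary and secondary objectives.** Add, for example: *The verdict is not given on the event count alone if a death within 30 days has been judged probably or definitely related to PITAC. Related deaths are reported on a separate line.*
2. **Interim analysis.** Unless the full protocol already provides for it, add: *A death judged probably or definitely related to PITAC brings the interim safety analysis forward, without waiting for the next 10-procedure look.* What follows from that review is for the sponsor to decide.

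Use the relatedness categories already in the objectives section. Adding possibly related deaths would depart from that filter and, in a population with a stated life expectancy of 3–12 months, would bring in deaths that cannot be clearly attributed.

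**Cost.** A few sentences, a verdict that is slightly harder to reach, and a short pause if such a death occurs. At an assumed related-death risk of 0.5% per procedure, the chance of at least one pause is 1 − 0.995^40 = 18% in 40 procedures and 1 − 0.995^60 = 26% in 60. These are chances of a review, not of stopping the study, and should not be set against the stopping probabilities above.

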## Results and discussion

### Hypothesis

Based on OPC´s experience with PIPAC and preliminary data from previously performed PITAC procedures, we expect that this study will show that PITAC is both feasible and safe for patients and the involved health care personnel.
